## Abstract

**Background:**

Corticosteroids are one of the few drugs that have shown a reduction in mortality in coronavirus disease 2019 (COVID-19). In the RECOVERY trial, the use of dexamethasone reduced 28-day mortality compared to standard care in hospitalized patients with suspected or confirmed COVID-19 requiring supplemental oxygen or invasive mechanical ventilation. Evidence has shown that 30% of COVID-19 patients with mild symptoms at presentation will progress to acute respiratory distress syndrome (ARDS), particularly patients in whom laboratory inflammatory biomarkers associated with COVID-19 disease progression are detected. We postulated that dexamethasone treatment in hospitalized patients with COVID-19 pneumonia without additional oxygen requirements and at risk of progressing to severe disease might lead to a decrease in the development of ARDS and thereby reduce death.

**Methods/design:**

This is a multicenter, randomized, controlled, parallel, open-label trial testing dexamethasone in 252 adult patients with COVID-19 pneumonia who do not require supplementary oxygen on admission but are at risk factors for the development of ARDS. Risk for the development of ARDS is defined as levels of lactate dehydrogenase > 245 U/L, C-reactive protein > 100 mg/L, and lymphocyte count of < 0.80 × 10^9^/L. Eligible patients will be randomly assigned to receive either dexamethasone or standard of care. Patients in the dexamethasone group will receive a dose of 6 mg once daily during 7 days. The primary outcome is a composite of the development of moderate or more severe ARDS and all-cause mortality during the 30-day period following enrolment.

**Discussion:**

If our hypothesis is correct, the results of this study will provide additional insights into the management and progression of this specific subpopulation of patients with COVID-19 pneumonia without additional oxygen requirements and at risk of progressing to severe disease.

**Trial registration:**

ClinicalTrials.gov NCT04836780. Registered on 8 April 2021 as EARLY-DEX COVID-19.

**Supplementary Information:**

The online version contains supplementary material available at 10.1186/s13063-022-06722-x.

## Background

Patients with coronavirus disease 2019 (COVID-19) infection are at risk of developing pneumonia, acute respiratory distress syndrome (ARDS), multi-organ failure, septic shock, and death. ARDS is a consequence of an alveolar injury producing diffuse alveolar damage. Cytokine storm is involved in the development of ARDS in COVID-19 patients [1]. This cytokine storm in COVID-19 is characterized by an excessive inflammatory response to SARS-CoV-2 caused by a dysregulated immune system of the host. Around 30% of COVID-19 patients with mild symptoms at presentation will progress to severe life-threatening disease largely due to ARDS [2]. Early control of the cytokine storm through therapies is essential to prevent mortality in patients with COVID-19 [3–5].

Corticosteroids such as dexamethasone inhibit the host’s excessive inflammatory response via its anti-inflammatory properties. Based on the Guidelines of the Society of Critical Care Medicine/European Society of Intensive Care Medicine (SCCM/ESICM), the use of systemic glucocorticoid therapy in ARDS is recommended for patients who are relatively early in the disease course (within 14 days of onset) and who have persistent or refractory moderate to severe ARDS (partial arterial pressure of oxygen/fraction of inspired oxygen [PaO2/FiO2] ratio < 200), despite initial management with standard therapies, including low tidal volume ventilation [6]. Corticosteroid treatment in ARDS was associated with a significant reduction in biomarkers of systemic inflammation, reduction in the duration of mechanical ventilation, and reduction in-hospital mortality [7–10]. In addition, the disease resolution is faster with early initiation of glucocorticoid (< 7 days) compared with late initiation.

Current COVID-19 Treatment Guidelines recommend the use of dexamethasone in patients who require respiratory support [11–14]. Results from the Randomized Evaluation of COVid-19 thERapY (RECOVERY) trial demonstrated a reduction in 28-day mortality with 6 mg daily of dexamethasone for up to 10 days compared to standard of care in patients hospitalized with COVID-19 who were receiving either invasive mechanical ventilation or oxygen alone at randomization [15]. Patients without respiratory support needs did not seem to benefit from corticosteroid use. Similarly, in a prospective meta-analysis that pooled data from seven randomized clinical trials of critically ill patients with COVID-19, systemic corticosteroid administration was associated with lower 28-day all-cause mortality compared with usual care or placebo [16].

An increase in inflammatory biomarkers is known to correlate with progression to ARDS and mortality in COVID-19 patients. Available data provide evidence for the differentiation of severe and non-severe cases of COVID-19 based on inflammatory biomarkers including lactate dehydrogenase (LDH), C-reactive protein (CRP), and lymphocyte count [17, 18]. Elevated LDH increase mortality (OR, 4.22; 95% confidence interval [95% CI], 2.49–7.14) in patients with COVID-19 [19]. For each 100-unit increase in CRP levels, the odds of death increase twofold (OR, 2.01; 95% CI, 1.57–2.56) [20]. Finally, a lymphocyte count lower than 0.95 × 10^9^/L is associated with a risk of death compared to patients with lymphocyte counts greater than 0.95 × 10^9^/L (OR, 7.27; 95% CI, 1.10–48.25) [21].

As mentioned above, in the RECOVERY trial, dexamethasone did not reduce mortality in patients with SARS-CoV-2 pneumonia without the need for supplemental oxygen. Nevertheless, we postulate that the use of corticosteroids in COVID-19 pneumonia in its initial phases might have a different effect in patients with inflammatory biomarkers associated with disease progression. One-third of COVID-19 patients with mild symptoms at presentation will develop severe illness, particularly patients in whom biomarkers associated with COVID-19 disease progression are detected. Therefore, we conducted a study to evaluate whether the early administration of dexamethasone in hospitalized patients with COVID-19 pneumonia without additional oxygen requirements in whom biomarkers with a strong correlate with severe prognosis are detected, leads to a decrease in the development of ARDS and death.

## Methods/design

### Justification of the study

Currently, dexamethasone is one of the few drugs that has shown a reduction in mortality in COVID-19 patients [15]. The RECOVERY trial found no benefit in patients with COVID-19 who did not require supplementary oxygen. Unfortunately, the RECOVERY trial did not collect laboratory biomarkers to predict the risk of the development of ARDS in these patients. Hence, the need for this study is based on the possibility that the benefit of dexamethasone in this specific subpopulation of patients was underestimated. Our goal in this study is to analyse dexamethasone’s efficacy in preventing the development of ARDS and death in patients with COVID-19 pneumonia who do not require respiratory support, and in whom biomarkers independently associated with increased risk of severe disease are detected.

### Study design

Effect of EARLY administration of DEXamethasone in patients with COVID-19 pneumonia without acute hypoxemic respiratory failure and risk of development of acute respiratory distress syndrome (EARLY-DEX COVID-19) study is a multicenter, randomized, controlled, open-label, parallel-group trial involving 252 hospitalized patients with COVID-19 pneumonia who do not require supplemental oxygen on admission, and laboratory biomarkers related to severe COVID-19 disease are detected. Patients will be randomized and enrolled in Spain. Study sites are listed in the Appendix.

The trial was designed in accordance with the Declaration of Helsinki [22], the Convention of the European Council related to human rights and biomedicine, and within the requirements established by Spanish legislation in the field of biomedical research, the protection of personal data, and bioethics, which was registered on 8 April 2021 at http://www.clinicaltrials.gov with identification no. NCT04836780. The study protocol (version 1.2, 17 April 2021) was approved by the Ethics Committee for investigation with medicinal products of the Comunidad de Madrid, Spain, and the institutional review boards of all participating hospitals (Additional file 1). The trial was approved by the Spanish Agency of Drugs and Medical Devices as a clinical randomized study with drugs on 25 May 2021 (Additional file 2 in Spanish).

Prior to any activity carried out as part of the research, subjects will receive a concise and focused presentation of key information about the clinical trial, verbally and with a written consent form. To be included, written informed consent will be requested from patients’ relatives or legal representative by the local investigators. Following the recommendations of the Spanish Agency of Medicines and Medical Devices, during the COVID-19 pandemic, patient consent can be obtained orally and preferably before an impartial witness, documenting it in the patient’s medical records [23]. The forms have been reviewed by the Ethics Committee that authorized the trial.

Our protocol followed the SPIRIT (Standard Protocol Items: Recommendations for Interventional Trials) guidelines [24]. See Additional file 3 for the SPIRIT checklist of the study protocol.

### Inclusion criteria

To be eligible for inclusion, patients must fulfil the following criteria during screening and prior to enrolment: hospitalized patients aged 18 years or older with confirmed SARS-CoV-2 pneumonia who do not require supplemental oxygen, and risk of developing ARDS. The risk of ARDS is defined by the presence of at least two of the following inflammatory biomarkers: LDH > 245 U/L, CRP > 100 mg/L, and lymphocyte count < 0.80 × 10^9^/L (Table 1).

**Table 1 Tab1:** Inclusion criteria

a) Adults (age 18 years or older)
b) Confirmed COVID-19 based on a positive RT-PCR test or rapid antigen test for SARS-CoV-2 RNA in a respiratory specimen (nasopharyngeal or nasal swab)
c) Requiring in-hospital care
d) A chest imaging study compatible with pneumonia (X-ray or computed tomography)
e) SpO2 ≥ 94% and < 22 bpm breathing on room air
f) The presence of at least two of the following inflammatory biomarkers:
• LDH > 245 U/L
• CRP > 100 mg/L
• Lymphocyte count < 0.80 × 10^9^/L

*Abbreviations: SpO2* Peripheral capillary oxygen saturation, *bpm* Breaths per minute, *LDH* Lactate dehydrogenase, *CRP* C-reactive protein

### Exclusion criteria

The exclusion criteria include one or more of the following: patients with a history of allergy to corticosteroids, need for supplementary oxygen, pregnancy or breastfeeding status, oral or inhaled corticosteroids treatment in the preceding 15 days, human cytochrome P450 (CYP) enzyme–inhibiting drug treatment, use of immunosuppressants or immune-modulators (including chemotherapy) in the preceding 30 days, neutropenia < 1.0 × 10^9^/L, human immunodeficiency virus infection with CD4 cell counts < 0.50 × 10^9^/L in the preceding 90 days, dementia, liver disease defined as alanine aminotransferase (ALT) or aspartate aminotransferase (AST) ≥ 5 times the upper limit of normal, chronic kidney disease defined as a glomerular filtration rate ≤ 30 mL/min, haemodialysis or peritoneal dialysis, uncontrolled infection, and participation in clinical trials of any kind in the previous 28 days.

### Randomization

Eligible, consenting patients will be randomly assigned in a 1:1 ratio to receive either dexamethasone plus standard of care (intervention group) or standard of care alone (control group). Randomization will be done within the REDCap system with unpredictability of assignments. Our statistician created a randomization schedule using a permuted block design, so equal numbers are assigned to each group. This system ensures a balanced allocation of subjects to the study arms. Records of individual assignments to each group will be de-identified (user number and centre ID instead of patients’ names), sequentially numbered, and stored on a secure computer system. Local investigators in participating centres are the only authorized personnel to interact with the radomization system through a username and password. Once eligibility is confirmed in the electronic case report form, the treatment group is assigned by the system. Dexamethasone will be provided free of charge for this study by the organization funding. According to the ethical principles for medical research of the Declaration of Helsinki, the use of no placebo (no intervention) is acceptable when no proven intervention exists. The Spanish Agency of Drugs and Medical Devices and the Ethics Committees did not mandate a blinded design or the administration of a placebo.

### Intervention

Patients in the intervention group will receive an intravenous dose of 6 mg once daily from day 1 to day 3, followed by an oral dose of 6 mg once daily from day 4 to day 7 (Fig. 1). For participants unable to take an oral drug, intravenous dexamethasone will be given. We selected the same dose as the RECOVERY trial. Participants randomized to the control group will receive a standard of care. Given that pulmonary disease can progress rapidly in patients with COVID-19, patients will be closely monitored. For improving intervention adherence, a real-time medication monitoring system will offer monitoring of participants’ medication control combined with a short message service (SMS) after discharge. Study participants will receive the best standard of care according to the current COVID-19 Treatment Guidelines. Hospitalized patients who do not require supplemental oxygen can receive anticoagulants for the prevention of venous thromboembolic disease, gastric ulcer prophylaxis, hydration, antipyretics, antibiotics, and bronchodilators. Corticosteroids in patients requiring oxygen support in the control group will be received. In addition, remdesivir, tocilizumab, baricitinib, tofacitinib, and sarilumab will be considered in case of a worsening of disease status [13]. All chronic medication prescribed to the patient is permitted to continue at the discretion of the responsible physician/investigator.

**Fig. 1 Fig1:**
[figure not shown]
Study design diagram

For a trial participant, the assigned study intervention will be modified or discontinued by trial investigators if serious adverse events occur during the study period or withdrawal of participant consent. Regardless of any decision to modify or discontinue their assigned intervention, study participants will be retained in the trial whenever possible to enable follow-up data collection and prevent missing data.

### Data collection and procedures study

All participating patients, regardless of the study arm into which they are randomized, will be monitored following general standard of care practices. Patients will be assessed once daily by local investigators.

Demographic data including age and sex assigned at birth, comorbidities, and the COVID-19 vaccination status from participants will be collected. Temperature, respiratory rate, cardiac frequency, peripheral capillary oxygen saturation (SpO2), respiratory support, partial pressure of arterial oxygen/fraction of inspired oxygen (PaO2/FiO2), quick Sequential Organs Failure Assessment (qSOFA) score, and the ordinal scale for clinical improvement of the World Health Organization will be monitored at least once daily. Biochemistry and haematological tests on days 1 and 7; and chest X-ray on days 1, 4, and 7; and discharge will be assessed (Table 2). Laboratory determinations will include haemoglobin, white blood cell, lymphocyte count, platelets count, glucose, blood urea nitrogen, serum creatinine, sodium, potassium, LDH, alkaline phosphatase, albumin, ALT, AST, total bilirubin, CRP, prothrombin time, D-dimer, ferritin level, interleukin-6, and procalcitonin. Patients will be followed up to 90 days after randomization.

**Table 2 Tab2:**
[figure not shown]
Scheduled protocol activities

*Abbreviations: SpO2* Peripheral capillary oxygen saturation, *PaO2* Partial pressure of arterial oxygen, *FiO2* Fraction of inspired oxygen, *qSOFA* Quick Sequential Organs Failure Assessment, *WHO* World Health Organization

^a^Haemoglobin, white blood cell, lymphocyte count, platelet count, glucose, blood urea nitrogen, serum creatinine, sodium, potassium, LDH, alkaline phosphatase, albumin, ALT, AST, total bilirubin, CRP, prothrombin time, D-dimer, ferritin level, interleukin-6, and procalcitonin

Safety of the intervention will be actively evaluated by daily interrogation of the following common adverse effects of dexamethasone: hyperglycaemia, steroid-induced psychosis, gastrointestinal bleed, new infection, and chorioretinopathy or blurred vision [25].

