### Safety assessment

All patients who have been randomized and have taken at least one dose of treatment will be analysed for safety. Safety outcomes include bleeding, metabolic complications (ketoacidosis, hyperglycaemic hyperosmolar state, hyperglycaemia requiring new use of insulin), hypertension, new cardiac arrhythmia, allergic reaction, psychiatric disorders, new infections, and chorioretinopathy or blurred vision. All adverse events occurring after entry into the study and until hospital discharge will be recorded in the patient’s health record. An adverse event that meets the criteria for a serious adverse event between study enrolment and hospital discharge will be reported to the local Institutional Review Board. A serious adverse event for this study is any untoward medical occurrence that is believed by the investigators to be causally related to the study-drug and results in any of the following: life-threatening condition, severe or permanent disability, prolonged hospitalization, or a significant hazard as determined by the Data Safety Monitoring Board. Serious adverse events occurring after a participant is discontinued from the study will not be reported unless the investigators feel that the event may have been caused by the study drug.

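### The effects asked about each day do not match the declared safety outcomes, and one is named by its presumed steroid cause, which leaves room for uneven ascertainment in an open-label trial

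*Protocol article*

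**What the plan says.** Safety information is described in two places.

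The paragraph after Table 2, within the data collection section, sets out active questioning: "Safety of the intervention will be actively evaluated by daily interrogation of the following common adverse effects of dexamethasone: hyperglycaemia, steroid-induced psychosis, gastrointestinal bleed". The items in full are "hyperglycaemia, steroid-induced psychosis, gastrointestinal bleed, new infection, and chorioretinopathy or blurred vision". That makes five, introduced as effects of the study drug. The paragraph does not say whether control patients are asked the same questions.

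The Safety assessment section then declares the safety outcomes: "Safety outcomes include bleeding, metabolic complications (ketoacidosis, hyperglycaemic hyperosmolar state, hyperglycaemia requiring new use of insulin", continuing with "hypertension, new cardiac arrhythmia, allergic reaction, psychiatric disorders, new infections, and chorioretinopathy or blurred vision". That makes eight groups. The same section adds a general duty: "All adverse events occurring after entry into the study and until hospital discharge will be recorded in the patient’s health record".

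Three other parts of the article bear on the point:

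- **Data collection.** Patients in both arms are monitored under standard of care. Local investigators assess patients once a day, and heart rate and qSOFA are recorded at least daily. The scheduled laboratory work, which includes glucose, is "Biochemistry and haematological tests on days 1 and 7".
- **Intervention.** Control patients who come to need oxygen support receive corticosteroids.
- **Discussion.** The lack of blinding and of a placebo is named as the major limitation.

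**The concern.** In an open-label trial, active questioning with a fixed list is the main protection against looking harder for steroid effects in patients known to be on the steroid. It protects only the outcomes on the list, and only if the wording lets an event count in either arm.

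An outcome that is declared but not solicited reaches the data when someone notices it and writes it down. Staff who know that a patient is on dexamethasone may be readier to notice and record raised blood pressure or a change in mood than they would be in a control patient. A between-arm difference in such an outcome would then mix true harm with differential ascertainment.

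A term that contains its own cause raises a further problem. To record a steroid-induced psychosis, the investigator must first attribute the episode to a steroid, and that judgement depends on knowing the treatment.

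The trial undertakes to report the incidence of adverse events, and it tests a drug in patients for whom benefit is unproven, so the safety comparison will carry weight.

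**Working it through.** The article states no figure on this point, so there is none to reproduce. The check sets the two lists side by side and then looks for other routes by which an unlisted outcome would be found.

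**Step 1. Item-by-item comparison**

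| Declared outcome group (Safety assessment) | Daily question (after Table 2) | Relation |
|---|---|---|
| New infections | New infection | Match |
| Chorioretinopathy or blurred vision | Same | Match |
| Metabolic complications, three named forms | Hyperglycaemia, no threshold | Partly covered |
| Bleeding, any site | Gastrointestinal bleed | Narrower |
| Psychiatric disorders | Steroid-induced psychosis | Narrower, and cause-laden |
| Hypertension | None | Not solicited |
| New cardiac arrhythmia | None | Not solicited |
| Allergic reaction | None | Not solicited |

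Count: 2 match + 1 partly covered + 2 narrower + 3 not solicited = 8.

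The metabolic row is not counted as a gap. A question about any hyperglycaemia is broader than the declared hyperglycaemia that needs new insulin, so it can bring up candidates for the outcome. It does not name ketoacidosis or the hyperosmolar state. The groups with a gap are therefore 2 + 3 = 5 of 8.

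**Step 2. Can a control patient meet the psychosis term?**

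Only after receiving a corticosteroid. The Intervention section provides for this when a control patient needs oxygen support. The Sample size section assumes a 30% risk of ARDS in the control group and plans 126 patients per group, so 0.30 × 126 = 37.8, or about 38 control patients. If all of them need oxygen, as one would expect, at least about 38 controls could meet the term at some time, and at most 126 − 38 = 88 never could. More controls may need oxygen without reaching ARDS, so the first number could be higher and the second lower. Even controls who receive a corticosteroid cannot meet the term before that point, whereas patients on dexamethasone can meet it from the first dose.

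**Step 3. Other routes of detection**

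- The duty to record all adverse events until discharge covers every declared outcome in principle.
- Daily investigator assessment, and monitoring regardless of arm, give regular occasions to notice events.
- Daily heart rate gives some signal for arrhythmia, and the daily qSOFA may add related information. The article presents neither as the means of detecting a declared safety outcome.

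These routes mean that the outcomes are not missed outright. They do not make noticing equal between arms, because the observer knows the allocation.

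**Step 4. Arm coverage**

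The monitoring statement covers both arms under general standard of care. The questioning is a separate activity, framed as evaluating the intervention, and its coverage is not stated.

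**The case against.** The strongest case against the point has five parts.

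- **The lists need not be identical.** Asking daily about a few common effects and collecting the rest as adverse events is a normal structure. This stands as a description of practice. It does not explain why an outcome declared as any bleeding is asked about only as gastrointestinal bleeding, or why a psychiatric outcome is asked about by its cause.
- **The unsolicited outcomes are still looked for.** A reader might infer that they are found only if staff happen to think of them. The document does not support that, given the recording duty, the daily assessment and the monitoring of both arms. Hypertension and arrhythmia are also found mainly by measurement rather than by questioning. This objection stands against the stronger reading. What remains is that the opportunity to notice is shared between arms, but readiness to notice and record may not be.
- **The psychosis term can apply to controls.** A reader might infer that it can never do so. That is wrong, because controls who need oxygen receive corticosteroids. The term remains unavailable to controls who receive none, and to the others until they do.
- **No size can be given.** One could assume detection of 90% on dexamethasone and 50% on control with an equal true rate, and obtain an apparent risk ratio of 0.90 / 0.50 = 1.8. That only returns the assumption. Nothing in the document supports those detection rates, so the figure is no evidence of the bias here.
- **The schedule in Table 2, the eCRF and the full protocol are not shown.** They may already align the lists and state that both arms are questioned. This stands, and it limits the point to an inconsistency between two lists that the article itself prints. If the working forms are aligned, a sentence of correction is enough.

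The two scheduled glucose tests might also be read as leaving hyperglycaemia undetected between days 1 and 7. That goes too far. The daily question is broad, monitoring follows standard of care, and new insulin use would be expected to appear in an inpatient's treatment record.

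**Conclusion.** The point holds as an inconsistency with a plausible but unquantified consequence. Of the eight declared safety outcome groups, three have no daily question and two are asked about more narrowly than declared. One of those two uses a term that presupposes steroid exposure. The article also leaves open whether control patients are questioned.

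The consequence is limited. These outcomes would still be recorded when noticed, and both arms are under observation. But noticing them rests on spontaneous recognition and routine care by unblinded staff, so a between-arm difference could partly reflect ascertainment.

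This assumes that the printed lists describe what is actually asked. That knowledge of the arm affects recognition is a recognised risk of the design and is not shown to have happened here. The protocol's defence of the open-label design, that its primary endpoint is clear, does not extend to investigator-recognised safety events. The point is minor and does not touch the primary analysis.

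**What to change.** Replace the daily list with the outcomes declared under Safety assessment, in words that carry no cause: for example, any bleeding (with site), and new psychosis or other psychiatric disorder. Add the three unsolicited groups. Leave any judgement of relation to the study drug to a separate field. State that the checklist is completed daily and identically in both arms. Count hyperglycaemia as an outcome only by the definition already declared.

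The cost is a slightly longer daily eCRF checklist, with no new tests or staff. The change concerns data collection only and alters no treatment rule.

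The same unblinded staff will complete the form, so the change reduces differential ascertainment without removing it, and the open-label caveat should stay in the report. Because recruitment began in June 2021, the date of the change should be recorded, so that events collected before and after it can be told apart. If the eCRF already uses the declared outcomes in both arms, only the article's text needs correcting.
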